#### Sample Size

The required sample size was a priori calculated using the G*Power software. Based on a previous experimental study analyzing the effects of framing and personalizing information about endocrine treatment on side-effect expectations in healthy women [14], a small-to-medium effect size can be expected for the impact of OIC on the primary outcome (treatment expectations). For two-tailed testing and a predetermined α level of .05, 106 participants would provide 80% power to detect significant interaction and the main effects of Cohen *f*=0.125 on the primary outcome. To compensate for an anticipated dropout rate of 15%, a total sample of 122 participants will be randomly assigned to one of the 2 groups (n=61 per group). Since it is assumed that at least 50% of all individuals can be included in the clinical trial after screening, approximately 244 individuals will need to be screened (see Figure 1).

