### Statistical Analyses

Linear mixed modeling for repeated measures will be conducted for the hypothesis referring to the primary outcome. Following the intention-to-treat approach, all randomized participants will be included in the analysis to avoid attrition bias. The model will contain one between-subject factor treatment (OIC + TAU vs TAU) and one within-subject factor time (T0, T1, and T2). Before linear mixed modeling, additional variables (eg, respective baseline scores, type of prior experiences with psychotherapy, prior knowledge about psychotherapy, satisfaction with the therapeutic relationship, state anxiety, the time of occupation with the information brochure) will be checked for significant associations with the respective outcomes to identify potential covariates. If there are additional covariates, they will be included in the linear mixed model. Group differences will be checked using Tukey posthoc tests. In case of imbalanced group sizes, Bonferroni-corrected posthoc tests will be carried out instead.

The analytical strategy of fitting linear mixed models will also be applied to all analyses, including secondary outcomes. Three exceptions for the described analytical strategy will be analyses including the secondary outcomes of capacity to consent, satisfaction with received information, and (serious) adverse events, for which group differences at postassessment will be examined by an independent sample two-sided *t* test, a Welch *t* test, or a Mann-Whitney *U* test. Intergroup differences at baseline will be detected using independent sample two-sided *t* tests, Welch *t* tests, or Mann-Whitney *U* tests (for continuous variables) and Pearson chi-square tests (for categorical variables). Partial eta squared will be reported for estimating the proportion of explained variance, with *η^2^*=0.01 indicating small, *η^2^*=0.06 indicating moderate, and *η^2^*=0.14 indicating large effects [40]. Cohen *d* will be determined as a measure of effect size for pairwise comparisons (standardized mean differences) by dividing the mean score difference between the groups to be compared by the pooled standard deviation. According to Cohen [40], values of *d*=0.2, *d*=0.5, and *d*=0.8 are considered to indicate small, medium, and large effect sizes, respectively.

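### Partial eta squared for the within-subject effects is read as explained variance and labelled with cut-offs for plain eta squared, so the reported size of the primary effect is inflated and depends on the correlation between visits

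*Protocol article*

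**What the plan says.** Under Statistical Analyses the article states: "Linear mixed modeling for repeated measures will be conducted for the hypothesis referring to the primary outcome". The model has a two-level treatment factor and a three-level time factor (T0, T1, T2), and the same strategy is extended to most secondary outcomes. On effect sizes, the section says that "Partial eta squared will be reported for estimating the proportion of explained variance", "with *η^2^*=0.01 indicating small, *η^2^*=0.06 indicating moderate, and *η^2^*=0.14 indicating large effects". It also plans Cohen d for pairwise comparisons, obtained by "dividing the mean score difference between the groups to be compared by the pooled standard deviation".

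Under Sample Size the trial is planned on Cohen f: "106 participants would provide 80% power to detect significant interaction and the main effects of Cohen" *f* = 0.125. No correlation between visits is given.

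The hypotheses at the end of the Introduction concern a greater change under OIC than under TAU from T0 to T2. In this model the treatment-by-time interaction carries that hypothesis.

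**The concern.** Two different quantities are treated as one. Eta squared is a share of total variance. Partial eta squared is a share of effect-plus-error variance. In a repeated-measures model the error term for time and treatment-by-time is the within-subject residual, from which stable differences between persons have been removed. For these effects partial eta squared is not the proportion of explained variance, and the same raw difference gives a larger value when the visits are more highly correlated.

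The cut-offs 0.01, 0.06 and 0.14 are written for plain eta squared. By f² = η²/(1 − η²) they correspond to f of about 0.10, 0.25 and 0.40, the scale on which f = 0.125 was planned. The trial would thus be sized on one scale and its main effect labelled on another. At stake is how large readers believe the OIC effect to be: a label could move from small to moderate because the questionnaire is stable over time, with no change in what OIC achieved.

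**Working it through.** **Inputs.** From Sample Size: f = 0.125, two-sided alpha 0.05, 80% power, 106 analysable participants. From Statistical Analyses: k = 2 groups, m = 3 time points. Assumed, because the article does not state them: the correlation ρ between visits, compound symmetry, and error degrees of freedom as in repeated-measures ANOVA.

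**1. Reproduce the plan's sample size.** For the interaction, λ = f²·N·m/(1 − ρ), df1 = (k − 1)(m − 1) = 2 and df2 = (N − k)(m − 1).

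- N = 106, ρ = 0.5: λ = 0.015625 × 106 × 3 / 0.5 = 9.94, df2 = 208, power 0.807.
- N = 104, ρ = 0.5: power 0.799, just short of 80%.
- With m = 3, ρ = 0.3 would need 146 participants and ρ = 0.7 would need 64.

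So 106 is reproduced exactly with three visits and ρ = 0.5. This makes ρ = 0.5 consistent with the plan's own figure, but it remains an inference.

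**2. The planned effect on the total-variance scale.** η² = f²/(1 + f²) = 0.015625/1.015625 = 0.0154, small by the article's cut-offs.

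**3. The same effect as partial eta squared.** Partial η² = λ/(λ + df2), with N = 106 and df2 = 208:

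| ρ | λ | partial η² | ratio to 0.0154 |
|---|---|---|---|
| 0 | 4.97 | 0.023 | 1.5 |
| 0.3 | 7.10 | 0.033 | 2.1 |
| 0.5 | 9.94 | 0.046 | 3.0 |
| 0.6 | 12.42 | 0.056 | 3.7 |
| 0.7 | 16.56 | 0.074 | 4.8 |
| 0.8 | 24.84 | 0.107 | 6.9 |

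A simulation of the 2 × 3 repeated-measures ANOVA (4,000 runs per setting) gave ratios of 2.9, 3.6 and 4.6 at ρ = 0.5, 0.6 and 0.7.

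**4. Where the label changes.** Partial η² = 0.06 requires λ = (0.06/0.94) × 208 = 13.28. Hence 1 − ρ = 4.969/13.28 = 0.374, and ρ is about 0.63. Below that the tabulated value stays in the small band; above it, the planned effect is called moderate.

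**5. How often a single trial would reach the moderate mark.** Partial η² ≥ 0.06 corresponds to F ≥ 6.64 on (2, 208) degrees of freedom. From the noncentral F distribution, a trial with exactly the planned effect reaches it with probability 0.37 at ρ = 0.5 and 0.71 at ρ = 0.7.

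**6. A larger effect.** At f = 0.25, η² = 0.0588. With ρ = 0.5, λ = 0.0625 × 318/0.5 = 39.75 and partial η² = 39.75/247.75 = 0.160, above the article's mark for large.

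**7. Sensitivity to the error degrees of freedom.** If a mixed model with unstructured covariance gave denominator degrees of freedom near N − 2 = 104 and partial η² were computed from F, the planned effect would show as 9.94/113.94 = 0.087 at ρ = 0.5 (5.7-fold) and 16.56/120.56 = 0.137 at ρ = 0.7 (8.9-fold).

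**The case against.** The strongest reply is that nothing inferential depends on these labels. Every hypothesis is tested two-sided at 0.05, and the model, alpha, sample size and p-values stay as they are. Cohen d is planned alongside with its own benchmarks, and a d on the pooled standard deviation does not carry this inflation. The word *partial* already signals effect-plus-error variance, so the gloss could be called loose wording. How the statistic is extracted from the mixed model, and with which covariance structure, is detail that an article may leave to its analysis plan. All of this limits the consequence. It does not remove the point: the article does state the reading and the cut-offs, and both are wrong for within-subject effects.

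Several stronger readings are tempting but not supported:

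- *An inflation of three- to fivefold as a fixed fact.* That range belongs to ρ between about 0.5 and 0.7 under compound symmetry. No correlation is stated. The plan's own N points to about threefold, at which the planned effect would still typically be called small.
- *That the rule labels a third of null effects as small.* With no effect, 35% of trials of 106 would reach 0.01 on the interaction, but this is largely sampling noise. An absolute d of at least 0.2 occurs in 31% of null trials of that size, and the group main effect reaches 0.01 equally often. Keeping subject variance in the denominator would lower the interaction rate to about 4% at ρ = 0.5. The rate is still not a fair headline against partial eta squared.
- *That the planned d uses raw group means and so carries chance baseline differences.* The text does not say which means are used; model-estimated or baseline-adjusted means fit it equally well.
- *That the observed value could never be compared with f = 0.125.* It can be converted once the correlation and the computation are known. It cannot be compared directly, as the labels invite.

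**Conclusion.** The point stands as an error in reporting and interpretation. The article equates partial eta squared with the proportion of explained variance and applies cut-offs from another scale. For time and treatment-by-time effects this gives a value above the total-variance share that depends on the visit correlation. At the planned effect and N = 106, the inflation is about threefold at ρ = 0.5 and about 4.8-fold at ρ = 0.7, with a range of 1.5- to 7-fold for ρ from 0 to 0.8. At ρ = 0.5, 37% of trials with exactly the planned small effect would be reported as at least moderate.

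These figures rest on compound symmetry and repeated-measures ANOVA degrees of freedom, neither of which the article states. The direction of the error holds across the whole range of ρ examined. It is worth correcting because the interaction carries the primary hypothesis and readers will judge OIC partly by its stated effect size.

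**What to change.** In Statistical Analyses, stop describing partial eta squared as the proportion of explained variance, and remove the 0.01/0.06/0.14 labels for time and treatment-by-time effects. As the main measure of effect, report the OIC-minus-TAU difference at T2 in scale points, adjusted for baseline, with its 95% CI, together with the corresponding d. State which means and which standard deviation that d uses; the pooled T0 standard deviation is one clear choice. If an explained-variance figure is still wanted, use generalized eta squared, which keeps between-person variance in the denominator and can be set beside the quoted cut-offs and f = 0.125.

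The cost is a sentence or two in the plan and minor reporting work, with no new data and no change to any test. The downside is that the reported effect size will look smaller.

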### TAU as a Comparator

To investigate the clinical significance of the newly developed OIC, a TAU condition will be used as a comparator. In both trial conditions, participants will receive an information brochure about psychotherapy from the Federal Chamber of Psychotherapists in Germany as TAU [30]. Participants may decide on their own whether and if so, how long they want to engage with the 80-page information brochure for psychotherapy patients.

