Missing values will be imputed using the multiple imputation technique but only if more than 2% of the data is missing. In case of multiple imputation, analyses will be repeated based on per-protocol analyses as a sensitivity analysis. If less than 2% of the data is missing, no multiple imputation will be carried out and a sensitivity analysis will be conducted using the last observation carried forward method. Each hypothesis will be tested two-sided with an α level of .05. All statistical analyses will be performed using SPSS version 27 (IBM Corp).

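### A per-protocol repeat is the named sensitivity analysis for multiple imputation, but it does not vary the missing-at-random assumption on which the intention-to-treat result rests

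*Protocol article*

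**What the plan says.** The Statistical Analyses section of the protocol article sets two branches by the amount of missing data. Above the threshold: "Missing values will be imputed using the multiple imputation technique but only if more than 2% of the data is missing". The check attached to that branch is: "In case of multiple imputation, analyses will be repeated based on per-protocol analyses as a sensitivity analysis". Below the threshold nothing is imputed, and the check is a different one: "a sensitivity analysis will be conducted using the last observation carried forward method".

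The Sample Size section gives the expected loss: "To compensate for an anticipated dropout rate of 15%, a total sample of 122 participants will be randomly assigned".

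The primary analysis is a linear mixed model with treatment and time (T0, T1, T2). It includes everyone randomised, and the stated purpose is protection against attrition bias. Under Procedure, randomisation takes place at the first visit (T0), and OIC is delivered at the second visit (T1) two weeks later, immediately before the post-assessment. Under Blinding, the article acknowledges that participants cannot be fully blinded. The primary outcome is a self-rated expectation score.

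**The concern.** A sensitivity analysis for missing data should change the assumption about the values nobody saw and show whether the conclusion survives. A per-protocol repeat does not do this. It restricts the analysis set and so answers a different question, about people who followed the protocol. The people whose scores are in doubt tend to leave the analysis altogether.

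The schedule makes this more than a formality. An OIC-arm participant who leaves between T0 and T1 never receives the consultation. If arm is in the imputation model, as is usual, that person's T1 and T2 scores are predicted from OIC participants who did attend. A per-protocol set would most naturally leave that person out. Neither analysis asks what happens if the leaver's expectations look like those in the TAU arm. If leavers did not benefit, both analyses would be too favourable together, and their agreement could be read as robustness.

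**Working it through.** **Inputs from the article.** N = 122 randomised (61 per arm), 106 before inflation, dropout 15%, f = 0.125, power 80%, two-sided alpha .05, primary time points T0, T1 and T2, imputation threshold 2%.

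**Assumed, because the article does not give them.** Correlation between repeated measures 0.5; when the 15% is lost; dropout by arm; the pattern of the effect over time; and arm being in the imputation model.

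**1. The plan's own figure.** For the group-by-time interaction, λ = f² × N × m / (1 − ρ) = 0.015625 × 106 × 3 / 0.5 = 9.94 with 2 and 208 degrees of freedom. Power is 0.807, and 106 is the smallest even N that reaches 80%. The result depends on the assumed correlation: N would be 146 at ρ = 0.3 and 64 at ρ = 0.7. The step to 122 is 106 × 1.15 = 121.9.

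**2. Which branch runs.** The primary model uses 122 × 3 = 366 scores, and 2% of these is 7.3. Anticipated dropouts number 0.15 × 122 = 18.3.
- Lost at T2 only: 18.3 / 366 = 5%.
- Lost at T1 and T2: 36.6 / 366 = 10%.
- Lost only at T3: none of the T0–T2 scores is missing (3.75% of T0–T3 scores).

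Eight missing T2 scores already exceed the threshold, fewer than half of the anticipated dropouts. If the losses fall by T2, the plan therefore runs multiple imputation with the per-protocol repeat. The article does not say which values make up the 2%; this count uses primary-outcome scores.

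**3. The size of effect behind f = 0.125.** Take no arm difference at T0 and an equal difference d at T1 and T2. The interaction effects in each arm are then d/3, d/6 and d/6 in absolute size. Their mean square is (4 + 1 + 1)/36 ÷ 3 × d² = d²/18, so f = d/√18 and d = 0.125 × √18 = 0.53 SD. A linear build-up from T0 to T2 gives d = 0.125 × √24 = 0.61 SD.

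**4. Leavers before T1.** Suppose 15% of the OIC arm (about 9 of 61) leave before T1 with no benefit, leaving is unrelated to the baseline score, and attenders gain d.
- Intention-to-treat effect: 0.85 × 0.53 = 0.45 SD.
- Imputation under missing at random: about 0.53 SD, because leavers are predicted from attenders. A completers-only analysis gives about the same.
- Gap: 0.15 × 0.53 = 0.08 SD (0.15 × 0.61 = 0.09 SD for the linear pattern).

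More generally, the gap is the OIC dropout share times the shift δ between true and imputed scores. At 15% dropout, δ = 0.25, 0.5 and 1.0 SD gives 0.04, 0.075 and 0.15 SD. At δ = 0.5 SD, dropout of 10% to 25% gives 0.05 to 0.125 SD.

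**5. Leavers after T1.** A large-sample simulation had no true effect, correlation 0.5, T0 and T1 observed, and 15% missing at T2 in each arm. TAU dropout was random. OIC dropout depended on the unseen T2 score, with log-odds of −1 to −2 per SD.

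| Analysis | Bias in the arm difference |
|---|---|
| Imputation under missing at random | +0.09 to +0.15 SD |
| Completers only (stand-in for per-protocol) | +0.13 to +0.21 SD |

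The observed T1 score removes part of the bias but not all of it, and both analyses err in the same direction. With the same dropout mechanism in both arms, both biases are about zero.

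**The case against.** The best reply is that this is a condensed article. A fuller plan may add analyses under other assumptions, and the article never says per-protocol is the only check or that it tests missing at random. That is fair for anything merely left out. It does not dispose of the point, because the article itself names the sensitivity analysis for the imputation branch, and the one named does not serve that purpose. Nor does the article use the term missing at random; the assumption is inferred from the methods it names.

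The size is also open to challenge. The article gives no dropout by arm or by visit. Someone who attends OIC and does not benefit normally has a T1 score on the same day, which the imputation uses. These objections stand, so the figures above are illustrations only. A reader might infer that the trial will overstate its effect by 18% (0.53 / 0.45). That needs all OIC-arm dropout to occur before any T1 score, with no benefit, and nothing in the article indicates this.

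Three further readings are tempting but not supported:
- **That last observation carried forward fails in the same way.** It does replace the missing-at-random assumption with a different one, and it sits in the branch below 2%, where missing data matter least.
- **That a per-protocol set would remove mainly OIC participants.** TAU participants are free to ignore the brochure ("Participants may decide on their own whether and if so, how long they want to engage"). However, the per-protocol set is not defined, and both arms have a T1 visit that can be missed.
- **That imputation should give way to a likelihood-only mixed model as primary.** That is a trade-off, and no harm from the present choice has been shown.

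**Conclusion.** The point holds in a limited form. At the article's own dropout figure, and if the losses fall by T2, the planned check on multiple imputation is a per-protocol repeat. That repeat leaves the assumption about unseen scores untouched and can err in the same direction as the imputation. Agreement between the two would not establish that the intention-to-treat result is robust.

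The possible size is modest: about 0.08 SD on an effect of 0.53 SD in the leave-before-T1 illustration. It rests on an assumed effect pattern, 15% loss in the OIC arm before T1, no benefit in leavers, and arm being in the imputation model. It is smaller when T1 scores are observed and about zero when dropout works alike in both arms. The documents do not show that such bias will occur. They show only that the named check could not reveal it. In the leave-before-T1 scenario a true effect of zero stays zero, so that mechanism can enlarge a real effect but not create one.

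**What to change.** Keep the mixed model and multiple imputation as primary. For the imputation branch, replace the per-protocol repeat as the missing-data sensitivity analysis with one or both of the following:
- **Delta-adjusted imputation.** Shift the imputed OIC-arm scores downwards in steps and report the shift at which the conclusion changes (the tipping point).
- **Reference-based imputation.** Let OIC-arm dropouts follow the TAU trajectory. This directly addresses those who leave between T0 and T1.

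Keep the per-protocol analysis, define its set, and label it supplementary.

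The cost is a change of wording and one extra imputation run on data already collected. Sample size and trial conduct do not change. The downside is that the sensitivity estimate may be smaller than the primary one.

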### Ethics Approval

This trial is performed in accordance with the Declaration of Helsinki and was approved by the local ethics committee of the Center for Psychosocial Medicine, University-Medical Center Hamburg-Eppendorf, Hamburg, Germany (reference: LPEK-0292, 01.04.2021). The data generated from this study will be available for scientific purposes in PsychArchives (a disciplinary repository for psychological science) [41]. All participants provide informed written web-based consent for participation and for the publication of anonymized data for scientific purposes in the disciplinary repository.

## Results

The first participant was enrolled on August 5, 2021. We expect to complete data collection in December 2022. After data analysis within the first quarter of 2023, the results will be submitted for publication in peer-reviewed journals in summer 2023. Research reports will be additionally disseminated through scientific forums, including presentations at conferences.

## Discussion

The aim of this two-armed randomized controlled superiority trial is to evaluate the efficacy of a newly developed OIC for psychotherapy under consideration of its legal, ethical, and clinical functionalities. In this trial, the effects of an OIC combined with TAU is compared to those of TAU alone in a sample of German adults with an indication for psychotherapy. OIC was developed under consideration of the latest empirical evidence concerning the legal, ethical, and clinical requirements of a truthful informed consent procedure, including possible strategies to promote and integrate these functions. A semistructured guideline with supportive visual information cards was developed. Since OIC will take relatively little time and does not require advanced professional trainings, it might be a cost-effective tool for daily practice.

Noteworthily, a genuine clinical approach for integrating risk information into the informed consent for psychotherapy has been missing to this day. If proven effective, future patients might be adequately informed about possible risks of psychotherapy without violating the ethical principle of nonmaleficence. This multifaceted evaluation of a structured OIC might help reduce the initial reservations of psychotherapists about informing patients about the possible negative effects. Thus, OIC may represent the first feasible approach of fulfilling the legal demands of informed consent in clinical practice.

The web-based context was chosen to enable the participation of citizens living in rural areas with limited capacity of health care services. Since OIC is not restricted to a certain therapeutic approach, its scope of application is broad. In line with the current implications from psychotherapy research [42,43], OIC might contribute to a theory-overarching dissemination of recent empirical evidence into the care system.

Nevertheless, this trial will have some limitations that need to be acknowledged. Although the web-based context should help expanding the spectrum of recruitment, it might also lead to the exclusion of potential participants who do not have a suitable internet connection. Moreover, no conclusions can be drawn regarding the specific efficacy of each of the 3 applied strategies, namely, contextualization, framing, and shared decision-making. However, if identified as efficient, the impact of each subcomponent of OIC may further be analyzed on a factorial basis.

To this day, efforts to implement risk information into informed consent for psychotherapy seem to be rather insufficient. The newly developed OIC for psychotherapy might contribute to bridging the gap between theoretically assumed ideals of truthful informed consent and practical realities.

